### Serious adverse event and adverse event reporting

An AE is defined as any untoward medical occurrence in the patients which does not necessarily have a causal relationship with this treatment. These are usually identified by the physicians during the follow-up.

A SAE is an AE that fulfills one or more of the following criteria:

Results in death;Is immediately life-threatening;Causes severe organ damage.

The baseline information including vital signs, previous medical history, routine blood testing, liver and kidney function, will be recorded in detail before the intervention. The index will be monitored and compared with the baseline periodically during the follow-up. Complaints from participants will be carefully recorded and physical examinations should be conducted if necessary.

Once the AE or SAE is identified, the therapeutic regimen will be adjusted accordingly. Description of the detailed event, time of occurrence, professional assessment of the severity, relationship with the study intervention, and time from occurrence to resolution/stabilization should be recorded in the case report form, which will also be reported to the principal investigator, hospital ethics committee and medical affair department. The detailed reasons will be explained to patients responsibly and the subsequent solution will be suggested from a professional perspective. Patients should be followed up until proper resolution.

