### Discontinue criteria of intervention

Severe liver and kidney function abnormality associated with the intervention (transaminase increase more than twice of the normal value);Severe blood testing abnormality: red blood cell, hemoglobin, white blood cell or platelet count <50% of the lower normal limit, or more than twice the upper normal limit;Severe allergic reactions or arrhythmias: severe hypertension (blood pressure > 220/120 mmHg) or hypotension (blood pressure < 80/60 mmHg) caused by intervention; or severe arrhythmias (heart rate < 50 beats/min, heart rate > 140 beats/min or atrial fibrillation) and sinus arrest; or respiratory disorder (oxygen saturation < 85%);Consciousness disorders: coma, delirium or convulsions.

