### Discontinue/withdraw criteria of patients

Pregnant;Poor compliance to the protocol;Serious complications or other severe diseases happen during the administration and the continuation shows little benefits;Significant disease progression and the discontinuation is necessary after evaluation;Meet the exclusion criteria (newly or already confirmed);Unable to receive the intervention as scheduled.

Participants will be included in the final statistical analysis if they accomplish three courses of treatment and evaluation, otherwise will be excluded.

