### Intervention and follow-up

During the 5-year treatment, patients will undergo oral administration of idebenone or placebo with a dosage of 30 mg each time, three times a day. Given idebenone is prescribed conventionally for cerebral infarction, cerebral hemorrhage, and atherosclerosis sequelae caused by brain dysfunction, the optimal dosage is recommended by the instruction of idebenone (30 mg per tablet, Shenwei, Qilu Pharmaceuticals, China). We also deliberated the administration according to preliminary literatures and clinical trials in the use of neurodegenerative disorders (27–29). Therefore, the dosage is fixed without setting dose gradient as control groups. The drug will be kept by blinded nurses, and distributed to patients according to the code. Routine blood testing and liver function will be monitored every 6 months during the administration. Once serious side effects occur, such as leukopenia, liver function damage or severe allergic reaction, participants should discontinue or withdraw from the trial. The follow-up evaluations of patients include the assessment of rating scales, blood testing and neuroimaging examinations. Movement Disorder Society-Unified Parkinson's Disease Rating Scale (MDS-UPDRS), Mini-Mental State Examination (MMSE), Montreal Cognitive Assessment (MoCA), Sniffin' Sticks test-16 (SS-16), 17-Item Hamilton Rating Scale for Depression (HAMD-17), Non-Motor Symptom Questionnaire (NMSQ) and Scales for Outcomes in Parkinson's Disease-Autonomic questionnaire (SCOPA-AUT) is used to quantify the progression of motor and non-motor symptoms. In view of the favorable improvement on neurodegenerative disease of idebenone, it is speculated that idebenone might ameliorate RBD symptoms as well (30). Therefore, we use REM sleep behavior disorder screening questionnaire (RBDSQ) to identify the influence. Plasma exosome-synuclein levels will be tested to provide convictive biomarkers for neurodegeneration. Several inflammatory cytokines and chemokines (interleukin-6 (IL-6), IL-8, IL-10, tumor necrosis factor-α (TNF-α), TGF-β, C-X-C motif ligand (CXCL) 12, C-X3-C motif ligand 1 (CX3CL1), C-C motif ligand (CCL) 3, CCL15 and CCL20) will be measured based on our previous investigation (31). The SNCA methylation will also be analyzed by bisulfite sequencing (32, 33). In addition, according to our previous publications, functional connectivity impairment and increased free water in the posterior substantia nigra are indicative imaging markers for phenoconversion (34–36). PET/MRI can also provide supplementary evidence for dopaminergic neurodegeneration, which is necessary for the participants in the follow-up evaluation.

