
### Outcome measures

The primary outcome is the comparison of conversion rate from iRBD to synucleinopathies between idebenone and placebo group, measured at 5-year of follow-up. Clinical symptoms will be evaluated by physicians using comprehensive rating scales. PET/MRI will be carried out to reflect the dopaminergic degeneration. The secondary outcome is the safety and tolerability of idebenone in the treatment of patients with iRBD. The objects for safety evaluation should contain all the participants that have been administrated with the experimental drug. Safety evaluation including the laboratory test results, the events of death and adverse reactions, will be recorded in detail and analyzed after the trial (Table 1).

**Table 1 T1:** Outcome measures taken at baseline and follow-up.

**Endpoint**		**Measure**	**Evaluating methods/criterion**	**Time points**
Primary	Effectiveness: 5-year conversion rate of iRBD into synucleinopathies	Rating scales	MDS-UPDRS, RBDSQ, MMSE, MoCA, SS-16, HAMD-17, NMSQ, SCOPA-AUT	Baseline, 1, 3, 5 years
		Blood testing	Biomarkers including neuronal exosomal α-synuclein, SNCA methylation, inflammatory cytokines and chemokines (IL-8, TNF-α, TGF-β, IL-10, IL-6, CXCL12, CX3CL1, CCL15, CCL3 and CCL20)	
		Neuroimaging examinations	(^18^F-FP-CIT) DAT-PET/ MRI	
Secondary	Safety and tolerability	Vital signs	Body temperature > 39.5°C, pulse rate <50 beats/min, blood pressure < 80/60 mmHg, blood pressure > 220/120 mmHg, oxygen saturation < 90%;	Every 6 months
		Electrocardiogram	Atrial fibrillation, complete atrioventricular block, sinus arrest, ventricular tachycardia, ventricular fibrillation, pathologic Q-waves, arched ST-segment elevation	
		Laboratory tests	The ratio of alanine aminotransferase to aspartate aminotransferase over twice the normal values after treatment, the creatinine over twice the normal value, glomerular filtration rate lower than 20 ml/min, red blood cell, hemoglobin, white blood cell and platelet count <50% of the lower normal limit or more than twice the upper normal limit	
		Adverse events	Result in death, are immediately life-threatening or cause severe organ damage	

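### The closed three-item SAE definition, repeated in Table 1, leaves some admissions, disabling events and medically important events out of the SAE comparison and is not reconciled with the side effects the protocol calls serious

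*Protocol article*

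**What the plan says.** The section on serious adverse event and adverse event reporting introduces the definition with "A SAE is an AE that fulfills one or more of the following criteria" and then gives three items: "Results in death;Is immediately life-threatening;Causes severe organ damage". There is no open-ended item, and severe organ damage has no threshold.

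Table 1, under outcome measures, carries the same three items as the whole criterion of its adverse-event row: "Result in death, are immediately life-threatening or cause severe organ damage". That row belongs to safety and tolerability, the only secondary endpoint.

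Two other sections use the word serious without referring to this definition:

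- Intervention and follow-up: "Once serious side effects occur, such as leukopenia, liver function damage or severe allergic reaction, participants should discontinue or withdraw from the trial".
- Withdrawal criteria for patients: "Serious complications or other severe diseases happen during the administration".

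The reporting section sends AEs and SAEs alike to the case report form and to the principal investigator, the ethics committee and the medical affairs department.

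**The concern.** Because the list is closed, an event that matches none of the three items is not an SAE, whatever its consequence for the patient. Admission or prolonged stay, persistent disability, congenital anomaly and other medically important events appear nowhere in the document as grounds for seriousness.

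The follow-up section meanwhile applies the word serious to three kinds of event that the definition does not name. Two sites could class the same leukopenia or allergic reaction differently, one reading the follow-up section and the other the SAE definition.

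At stake is the SAE comparison between arms over five years of treatment. If an imbalance consisted mainly of admissions, disabling events or neurological events that were not immediately life-threatening, an SAE count built as written could miss it.

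**Working it through.** The definition involves no formula, so the check sets the sections side by side. For each event: must it meet one of the three SAE criteria, and if not, does another Table 1 row catch it?

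| Event | Where the protocol names it | Must it meet an SAE criterion? | Other Table 1 row |
|---|---|---|---|
| Leukopenia | Follow-up section, as serious | No | Laboratory, only if white cells are below 50% of the lower limit |
| Liver function damage | Follow-up section, as serious | Only if judged severe organ damage (no threshold given) | Laboratory, through its liver-enzyme criterion |
| Severe allergic reaction | Follow-up section, as serious; discontinuation criteria | Only if immediately life-threatening or organ-damaging | None |
| Delirium, convulsion | Discontinuation criteria | No | None |
| Atrial fibrillation | Discontinuation criteria | No | Electrocardiogram |
| Blood pressure above 220/120 mmHg | Discontinuation criteria | No | Vital signs |
| Coma, sinus arrest | Discontinuation criteria | Usually, as life-threatening | Sinus arrest: electrocardiogram |
| Admission or disabling event | Not named | No | Only if a vital-sign, ECG or laboratory threshold is also met |

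**Reading the table.**

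1. Of the three events called serious in the follow-up section, none qualifies automatically. Leukopenia need not qualify at all; the other two qualify in some cases only.
2. Of the four further categories (admission, disability, congenital anomaly, other medically important event), none is in the list.
3. The events with neither an assured SAE label nor another row are delirium, convulsion, severe allergic reaction, and admissions or disabling events that cross no measured threshold.

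**An illustrative ceiling for admissions.** The documents give no admission rate, so this rests on an assumed 3% to 10% of patients per year. Take the sample size section's 5-year conversion of 47% and 25%, 71 patients per arm, constant hazards, no drop-out, and follow-up ending at conversion or year 5.

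- Hazard = −ln(1 − p)/5: placebo −ln(0.53)/5 = 0.1270 per year; idebenone −ln(0.75)/5 = 0.0575 per year.
- Mean follow-up = p/hazard: 0.47/0.1270 = 3.70 years; 0.25/0.0575 = 4.35 years.
- Person-years: 71 × 3.70 ≈ 263 and 71 × 4.35 ≈ 308, about 571 in total.
- Admissions: 571 × 0.03 ≈ 17; 571 × 0.10 ≈ 57.

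These 17 to 57 are all admissions, including those already SAEs because they are life-threatening or organ-damaging. They are an upper bound on admissions lost from the SAE count, under an assumed rate, and the point does not depend on them.

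**The case against.** Most of the case against a stronger reading stands.

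- **Discontinuation criteria.** A reader might infer that these contradict the SAE definition, since they stop treatment for events such as "Consciousness disorders: coma, delirium or convulsions". They do not. They are stopping rules and speak of severity. Severity, seriousness and grounds for stopping are separate ideas, and stopping for a non-serious event contradicts nothing. The mismatch in wording is with the follow-up section.
- **Events going uncounted.** A reader might infer that every such event would be lost as an SAE. Coma, sinus arrest or oxygen saturation below 85% would usually count as life-threatening, and some allergic or liver events would qualify.
- **Loss of safety data.** A reader might infer a gap in reporting. AEs and SAEs share one route, the outcome section says adverse reactions will be recorded and analysed, and Table 1 catches atrial fibrillation, extreme blood pressure and marked blood-count changes in other rows. What is affected is the SAE label and the comparison built on it.
- **A conclusion fixed in advance.** The discussion's favourable remark on safety is background on the drug, not an anticipated result of this trial.
- **Outside standards.** The protocol cites none for seriousness, so comparability with other trials cannot be judged from it. Congenital anomaly is also remote at ages 40–75, although pregnancy is a listed withdrawal reason.

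One defence fails: that this is detail left to a fuller protocol. The article states the definition completely and gives it twice.

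**Conclusion.** The point holds in limited form. The SAE definition is a closed list of three, repeated as the adverse-event criterion of the only secondary endpoint, and is not reconciled with the events the follow-up section calls serious. Followed as written, it classes as non-serious any admission, lasting disability or other medically important event that does not also meet one of the three.

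The loss lies in SAE classification and in comparing the arms on events with no other Table 1 row. Recording, reporting and the primary endpoint are unaffected. The conclusion rests on the text alone. No reliable number can be attached to it, since the documents give no event rates. It merits correction because it weakens the safety comparison and can be put right by classification alone.

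**What to change.** 1. In the SAE definition and in the adverse-event row of Table 1, add in-patient hospitalisation or its prolongation, persistent or significant disability, congenital anomaly, and other medically important events.
2. Reconcile the list with the follow-up section, so that it is clear whether the events called serious there are SAEs and on what ground. This concerns classification only; no dose, visit, test or stopping rule need change.
3. Have blinded investigators re-code the events already recorded under the revised list before unblinding. Re-coding after unblinding would be open to bias.
4. In the same amendment, correct the abbreviations list, which expands AE as if it meant a serious adverse event.

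The cost is a protocol amendment, more events carrying SAE paperwork, and the re-coding. The case report form items listed in the reporting section do not name admission or disability, so source records at the three centres may need checking, for events as far back as July 2020.

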### Sample size and statistical analysis

The 5-year conversion rate of participants treated with idebenone is expected to decrease from 47% in the placebo group to 25%. The idebenone and placebo group are randomized at a ratio of 1:1, and a 5% drop-out rate is considered throughout the study. We estimated that 71 patients would be needed in each treatment group to allow for a power of 80% at two-sided α-level of 5%. In total, 142 patients are projected to be enrolled.

Statistical analysis will be performed using SPSS 27.0, STATA 17.0 and GraphPad Prism 9.4.0. Data will be analyzed on an intention-to-treat basis using two-sided tests with *p* < 0.05 considered significant. Continuous variables will undergo normality test as well as ANOVA test for inter-group comparison. Categorical variables will be compared using Chi-square test, Fisher's exact test or Wilcoxon rank-sum test. To assess the five-year conversion rate from iRBD diagnosis to clinically diagnosed synucleinopathies between patients treated with idebenone and placebo, we estimated the hazard ratio (HR) using a Cox proportional hazards model. Kaplan-Meier method will be applied to estimate median progression-free survival (PFS) and corresponding 95% confidence interval (CI) and survival curves will be plotted.

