**Methods:**

The EITRS study is a randomized, double-blind, multi-center clinical study assessing the efficacy and safety of idebenone in the treatment of iRBD into synucleinopathies. One hundred forty-two patients (aged 40–75 years old) with clinically diagnosed iRBD are planned to be recruited with 80% statistical power and randomly assigned to idebenone (30 mg each time, three times a day) or matching placebo orally for 5 years. The assessment of rating scales, blood testing and neuroimaging examinations will be conducted at baseline, the 1st, 3rd and 5th year of follow-up. The primary efficacy endpoint is the 5-year conversion rate in patients with iRBD. The secondary endpoint is the safety and tolerability of idebenone in the treatment of iRBD. The study has been launched in July 2020.

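### The 71 per group equals the number needed with no drop-out; if the stated 5% drop out and contribute no data, power at 142 is about 78–79%, not 80%

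*Protocol article*

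**What the plan says.** The section on sample size and statistical analysis gives every input. The five-year conversion rate "is expected to decrease from 47% in the placebo group to 25" per cent with idebenone. "The idebenone and placebo group are randomized at a ratio of 1:1", and the test is "at two-sided α-level of 5" per cent. On loss, "a 5% drop-out rate is considered throughout the study". The result is "We estimated that 71 patients would be needed in each treatment group to allow for a power of 80" per cent, followed by "In total, 142 patients are projected to be enrolled". The abstract repeats the claim: the 142 patients "are planned to be recruited with 80% statistical power".

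For the five-year conversion comparison, the same section says "we estimated the hazard ratio (HR) using a Cox proportional hazards model", on an intention-to-treat basis. The section on criteria for discontinuing or withdrawing patients says instead that participants who do not complete three courses of treatment and evaluation are left out of the final analysis.

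**The concern.** Since 142 is 2 × 71, the 71 is the number enrolled, and no allowance is added to it. Yet 71 is also what a standard formula gives when nobody drops out. If the 5% was mentioned but never used, the article claims a power that its own assumptions do not produce. The claim appears twice, and someone interpreting a null result would rely on it. There is no spare margin, because the calculation already assumes that conversion nearly halves.

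**Working it through.** **Inputs** (sample-size section): p₁ = 0.47, p₂ = 0.25, difference 0.22, 1:1 allocation, two-sided α = 0.05, power 80%, drop-out 5%. Hence (1.960 + 0.842)² = 7.849 and the mean conversion rate is 0.36. The article names no formula, so the usual candidates are tried.

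**1. Reproducing 71 without drop-out**

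- Unpooled two proportions: 7.849 × (0.47 × 0.53 + 0.25 × 0.75) / 0.22² = 7.849 × 0.4366 / 0.0484 = 70.8, i.e. 71 per group.
- Schoenfeld events formula: under proportional hazards HR = ln 0.75 / ln 0.53 = 0.453. Events = 4 × 7.849 / (ln 0.453)² = 50.1, and 50.1 / 0.36 = 139.2 patients in total. With events rounded up to 51, 51 / 0.36 = 141.7, i.e. 142 in total or 71 per group.
- Pooled two proportions (chi-square): 73.5, i.e. 74 per group.

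**2. Adding 5% drop-out by dividing by 0.95**

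- Unpooled: 70.8 / 0.95 = 74.5, i.e. 75 per group.
- Schoenfeld: 139.2 / 0.95 = 146.5 in total, about 74 per group (75 if events are first rounded up to 51).
- Pooled: 73.5 / 0.95 = 77.4, i.e. 78 per group.

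**3. Power with 71 enrolled per group**

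If drop-outs contribute nothing, 71 × 0.95 = 67.45 per group remain.

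| Formula | No drop-out (71) | 5% lost (67.45) |
|---|---|---|
| Unpooled two proportions | 80.1% | 78.1% |
| Schoenfeld | 80.8% | 78.8% |
| Pooled chi-square | 78.6% | 76.5% |

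For example, unpooled at 67.45: standard error = √(0.4366 / 67.45) = 0.0805, and Φ(0.22 / 0.0805 − 1.960) = Φ(0.774) = 78.1%. Schoenfeld at 67.45: events = 134.9 × 0.36 = 48.6, and Φ(√48.6 × 0.792 / 2 − 1.960) = Φ(0.798) = 78.8%.

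**4. Drop-outs as censored observations**

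Take constant hazards over five years: 0.127 per year on placebo (−ln 0.53 / 5), 0.0575 on idebenone (−ln 0.75 / 5), and 0.0103 for loss (−ln 0.95 / 5). The probabilities of an observed conversion fall from 0.470 and 0.250 to 0.459 and 0.244, with mean 0.352. Schoenfeld then needs 50.1 / 0.352 / 2 = 71.2 per group, and 71 per group has 79.9% power. If the 5% is spread over the six-year study duration instead, the number is 70.96 per group.

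**The case against.** The strongest defence is step 4. The conversion comparison is assigned to a Cox model on an intention-to-treat basis. In that analysis a patient who leaves is censored and counts until then, so dividing by 0.95 is too harsh, and 71 with drop-out included is attainable. This stands as a possibility. A reader might infer that no method yields 71 once drop-out is allowed for, or that the 5% was demonstrably ignored. Neither can be maintained, since the article names no formula and a condensed article may leave that to the full protocol. The defence is weakened by two things: the article does not describe such a calculation, and its rule excluding non-completers denies them the partial follow-up on which the calculation depends. That rule also sits badly with the intention-to-treat statement, and the article does not settle which applies.

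A reader might also quote a larger shortfall, such as 76.5% from the pooled chi-square or 71% from Fisher's exact test with 67 per group. The article lists those tests for categorical variables in general and names Cox for the conversion comparison. Moreover, the pooled chi-square has only 78.6% power at 71 per group with no drop-out, so about half of the distance from 80% to 76.5% comes from changing formula, not from loss.

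Finally, the gap is small beside the uncertainty in the assumed effect. With idebenone at 24% instead of 25%, unpooled power at 67.45 per group is Φ(0.23 / √(0.4315 / 67.45) − 1.960) = 82.0%. That is true and limits the importance of the point, but it does not make the stated figure right for the stated inputs.

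**Conclusion.** The concern holds in a limited form. The enrolled number coincides with the no-drop-out requirement by the unpooled formula (70.8) and by Schoenfeld with events rounded up. Under the usual allowance, 74 to 75 per group would be needed. If 5% drop out and contribute no data, power at 142 is about 78% (unpooled) to 79% (Schoenfeld), a shortfall of one to two percentage points. It would be 76.5% only if the primary test were a pooled chi-square.

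This rests on 47% v 25%, five years of follow-up per patient, proportional hazards for the Schoenfeld figures, and drop-outs contributing nothing. If drop-outs are instead censored evenly over follow-up, power is 79.9% and the shortfall practically disappears. That the 5% was not applied is an inference from the match at 71, supported by the exclusion rule; it is not a demonstrated fact.

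**What to change.** Enrol no more patients: recruitment was scheduled to close in July 2021. Restate the power in the abstract and in the sample-size section, using one named formula for both figures. For example:

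> For 47% v 25% at two-sided 5%, 142 randomised patients give 80% power with no drop-out and about 78–79% if 5% drop out and contribute no data.

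The matching pairs are 80.1% and 78.1% (unpooled), or 80.8% and 78.8% (Schoenfeld). An 80% no-drop-out figure should not be set beside 76.5%, which belongs to a different formula.

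If the sponsor used a calculation that censors drop-outs, the article should name it, state its loss assumption, and reconcile it with the rule that leaves non-completers out of the final analysis.

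The cost is a few words and a slightly less favourable stated power. The design and the analysis do not change, unless reconciling the exclusion rule leads the sponsor to revise it.

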## Background

Rapid eye movement (REM) sleep behavior disorder (RBD) is a parasomnia characterized by dream enactment behaviors and the loss of physiological muscle atonia during REM sleep (1). RBD has been categorized into idiopathic RBD (iRBD) and symptomatic forms, the latter of which is acknowledged as a precursory sign of α-synucleinopathies, including Parkinson's disease (PD), dementia with Lewy bodies (DLB), and multiple system atrophy (MSA), etc. (2). α-synucleinopathies are a group of neurodegenerative disorders characterized by aggregates of α-synuclein in neurons and glia, in the form of Lewy bodies, Lewy neurites, neuronal cytoplasmic inclusions, and glial cytoplasmic inclusions (3). More than 80–90% of iRBD patients ultimately develop a clinically defined neurodegenerative disease over longitudinal follow-up (4). Consequently, iRBD is considered as a recognizable preclinical state to enable the identification of individuals at risk of neurodegeneration (5). However, the pathogenesis and the potential mechanism still need investigation with little understanding of the reliable biomarkers of phenoconversion, which hinders the early diagnosis and intervention. Recent animal models and brain imaging researches revealed the degeneration of the core brain stem circuits controlling REM sleep in RBD pathology (6, 7). The initial REM sleep atonia loss (RSWA) and RBD symptoms accord with the pathological progression of Lewy body in PD which begins in the medulla and pons (8–10). It is speculated that α-synuclein could begin in the caudal brain stem affecting REM sleep circuits and progressively propagate to substantia nigra and other brain region (11). Besides, iRBD patients frequently exhibit specific neurodegenerative biomarkers, including: (1) clinical symptoms of hyposmia, constipation, orthostatic hypotension, cognitive decline, and gait initiation abnormalities; (2) structural or functional magnetic resonance imaging (MRI) signifying decreased nigrostriatal putamenal dopaminergic uptake, altered neuromelanin signal intensity and cortical thinning, as well as the brain glucose metabolism measured by ^18^F-FDG PET positron emission tomography (^1^8F-FDG PET) and dopamine transporter deficit by ^123^I-N-ω-fluoropropyl-2β-carbomethoxy-3β-(4-iodophenyl) nortropane single-photon emission computed tomography (^123^I-FP-CIT SPECT); (3) neurophysiological markers such as electroencephalographic slowing, etc (5, 12, 13). The signs may be important predictors for impendent phenoconversion, while the application should be integrated considering higher sensitivity and specificity.

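### ANOVA, the only method named for continuous outcomes, has no baseline term, although these outcomes are measured at baseline and three follow-up visits to track progression

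*Protocol article*

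**What the plan says.** The protocol article, under Sample size and statistical analysis, gives one method for comparing continuous variables between groups: "Continuous variables will undergo normality test as well as ANOVA test for inter-group comparison". It mentions no baseline covariate, change score or repeated-measures structure.

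Table 1 (Outcome measures) lists the measures concerned under the effectiveness endpoint. They are eight rating scales ("MDS-UPDRS, RBDSQ, MMSE, MoCA, SS-16, HAMD-17, NMSQ, SCOPA-AUT"), blood biomarkers and DAT-PET/MRI, each scheduled at baseline and years 1, 3 and 5. The section Intervention and follow-up says the scales serve to quantify how motor and non-motor symptoms progress, and that RBDSQ serves to detect an influence of idebenone on RBD symptoms.

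For conversion, the article says "we estimated the hazard ratio (HR) using a Cox proportional hazards model". It lists no covariates and does not call the model unadjusted. On clinical, imaging and neurophysiological markers, the Background says: "The signs may be important predictors for impendent phenoconversion". It gives no hazard ratio or correlation for any of them.

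The sample size rests on conversion alone: "expected to decrease from 47% in the placebo group to 25"%, with "71 patients would be needed in each treatment group to allow for a power of 80% at two-sided α-level of 5"%.

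**The concern.** Progression is movement from a starting point, and the named test has no term for that starting point. In outcomes such as cognitive scores or transporter binding, part of the variation between patients at follow-up is usually variation that was already there at baseline. ANOVA of a follow-up value leaves that part in the error term. A separate ANOVA at each visit also ignores the link between visits on the same patient.

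What is at stake is the precision of the supporting evidence on symptoms, biomarkers and imaging. With 71 patients per arm, wide intervals on these measures could hide an effect or leave an uncertain one uninterpretable. A further risk is conditional. If assessments stop when a patient converts, a year-5 comparison would contain only non-converters, so the groups would be selected on the primary outcome.

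The same reasoning extends, more weakly, to the Cox model. The article itself names markers it regards as predictive and measures several of them at baseline.

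**Working it through.** **1. The plan's own sample size.** Inputs from Sample size and statistical analysis: 47% v 25% at 5 years, 1:1 allocation, two-sided 5%, 80% power.

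- Implied hazard ratio under exponential times: ln(0.75)/ln(0.53) = 0.453.
- Events by Schoenfeld: 4 × (1.960 + 0.842)² / (ln 0.453)² = 50.1, rounded up to 51.
- Patients: 51 / 0.36 = 141.7, where 0.36 is the mean of 0.47 and 0.25. This gives 71 per arm and reproduces the stated figure before any allowance for loss. The unpooled two-proportion formula also gives 71.
- With 5% loss: 0.95 × 71 × (0.47 + 0.25) = 48.6 events, and power 78.8%.

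This calculation uses the conversion endpoint only. No continuous measure enters it.

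**2. Continuous measures: ANOVA against baseline adjustment.** Let rho be the correlation between the baseline and follow-up value. ANCOVA has residual variance (1 − rho²) times that of ANOVA on the follow-up value. For a comparison with 80% power under ANOVA, power under ANCOVA is Φ(2.802/√(1 − rho²) − 1.960).

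| Assumed rho | Variance factor | Variance reduction | Power, starting from 80% |
|---|---|---|---|
| 0.3 | 0.91 | 9% | 83.6% |
| 0.5 | 0.75 | 25% | 89.9% |
| 0.7 | 0.51 | 49% | 97.5% |

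The 80% starting point only sets a scale. The article claims no power for these measures.

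**3. If ANOVA means change scores.** Assuming equal variances at both visits, a change score has variance 2(1 − rho) relative to the follow-up value: 1.4, 1.0 and 0.6 at the three correlations. The ANCOVA factors are 0.91, 0.75 and 0.51, lower in each case.

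**4. Selection at year 5.** Under the design rates, the non-converters at year 5 are 1 − 0.47 = 53% of placebo and 1 − 0.25 = 75% of idebenone. This matters only if assessments stop at conversion. Endpoint criteria lists conversion as an endpoint but does not say that they stop.

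**5. Cox model.** Simulation with 71 per arm, marginal 5-year rates held at 47% and 25%, 5% loss, one standard-normal baseline covariate, exponential event times and 4,000 trials per setting:

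| Assumed HR per SD | Unadjusted power | Adjusted power | Gain (points) | Conditional treatment HR |
|---|---|---|---|---|
| 1.00 | 77.8% | 77.6% | −0.2 | 0.453 |
| 1.22 | 77.5% | 77.8% | +0.3 | 0.450 |
| 1.49 | 78.6% | 80.5% | +1.9 | 0.440 |
| 1.82 | 78.1% | 83.5% | +5.4 | 0.424 |
| 2.23 | 78.2% | 87.6% | +9.4 | 0.402 |
| 2.72 | 78.7% | 91.7% | +13.0 | 0.376 |

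Monte Carlo error is about 0.7 points for each power. Event times were treated as continuous although assessments fall at years 1, 3 and 5, and only one covariate was modelled.

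**The case against.** **The ANOVA sentence is brief.** It does not say which variables, which visit, or whether raw values or changes are compared. It could cover a baseline table, change scores or repeated-measures ANOVA, and the adverse event section does compare safety indices with baseline. This is fair, and it is why the point is about method rather than error. It does not remove the point. ANOVA is the only method given for these outcomes, and step 3 shows that adjustment does at least as well as change scores.

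**Nothing powered is touched.** This stands. The primary outcome is conversion and the secondary outcome is safety and tolerability. The scales, biomarkers and imaging have no sample size of their own.

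**A reader might infer more about the primary analysis:** that the Cox comparison ignores baseline and gives up several points of power for nothing. The article does not support this, for four reasons.

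- It is silent on covariates. It does not describe a treatment-only model, and a covariate list commonly sits in an analysis plan that is not shown here.
- It gives no prognostic strength. A gain of several points needs an assumed hazard ratio per SD clearly above 1.5, and a weak predictor gains nothing.
- Adjustment is not free. It changes the estimated effect from marginal to conditional, and about 51 events support only a few covariates.
- Chance imbalance after randomisation adds noise. It does not make an unadjusted analysis biased.

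**The year-5 selection problem** is likewise conditional, because the article does not say that assessments stop at conversion.

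**Conclusion.** The point holds for the continuous outcomes. The stated method leaves out baseline information that the trial collects in order to measure progression, and a baseline-adjusted model is a better choice at any non-trivial correlation. The variance reduction against ANOVA of follow-up values is 9% to 49% over assumed correlations of 0.3 to 0.7. The stated 80% power for conversion is not affected.

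For the Cox model, only a supporting suggestion is justified: confirm what the model contains, or pre-specify it. The likely gain runs from nil to about 9 points over assumed hazard ratios per SD of 1.0 to 2.2. The documents do not show where in that range the trial lies.

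**What to change.** For follow-up comparisons of continuous measures, replace ANOVA with one of the following:

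- ANCOVA with the baseline value as covariate, for a single visit; or
- a mixed model for repeated measures with baseline, visit, treatment and treatment-by-visit, using every available visit including the one at which conversion is found.

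State whether assessments continue after conversion. If they stop, the mixed model still uses the earlier visits of converters, under a missing-at-random assumption, where a year-5 ANOVA would drop those patients. The sentence under Discontinue/withdraw criteria of patients that removes those without three courses of treatment and evaluation would also take visits out of this model. It needs reconciling with the intention-to-treat statement.

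For the Cox model, confirm the covariates if they are already fixed elsewhere. Otherwise pre-specify a small number that the article itself points to, for example baseline DAT-PET and SS-16, and report the unadjusted hazard ratio beside the adjusted one.

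The cost is analysis-plan wording, settled before unblinding, with no new patients, visits or measurements. The small downside is that the adjusted hazard ratio is a conditional effect and must be labelled as such.
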